### Discontinuation of Study Subject Participation

Necessary testing will be carried out to assess the efficacy and safety of the Amitose DGA-containing cream if its use is permanently discontinued due to termination of subject participation in the study. Participants can be withdrawn from the study if their consent is withdrawn; if inadequacies are found after enrollment; if sunitinib therapy is determined to be unnecessary because of RCC resolution; or if the patient is unable to continue sunitinib therapy because of disease progression, complications, or adverse events induced by sunitinib or Amitose DGA-containing cream. Participation can be terminated in cases of pregnancy, noncompliance with the use of the investigational preparation (ie, compliance ratio less than 70%), if the study is discontinued, or if other issues emerge that warrant study discontinuation, according to the physician.

### Statistical Plan

All analyses will be conducted using SPSS Statistics for Windows, version 24.0 (IBM Corp) or later. Interim analyses will be not performed.

#### Sample Size Calculation

Participants were enrolled in the Phase I cohort group until the sample size reached 5 patients, in the event that study discontinuation occurred before the use of the investigational preparation. The sample size for the Phase I study was primarily based on the extent of necessity and concernment. To limit the potency of intolerable adverse events, the investigational preparation is an ascorbic acid derivative, which is generally equivalent to cosmetic preparations; however, there are no practical safety data pertaining to the administration of Amitose DGA-containing cream to patients with RCC receiving sunitinib therapy. In this study, the safety of Amitose DGA has been confirmed by a cohort of 5 patients.

The sample size for the Phase II study will be 30 participants, in combination with the Phase I study sample (ie, 5 Phase I participants and 25 additional participants). In previous reports from our institution, HFSR of any grade (ie, grades 1-3) was 33.3%; HFSR of grade 3 was 2.2% among patients with metastatic RCC who were treated with a 2-week-on and 1-week-off sunitinib schedule [18]. Given that the investigational preparation can prevent up to 75% of grade 1-2 HFSR, we estimate that the frequency of HFSR of any grade (ie, grades 1-3) among patients using the investigational preparation will be 10%. In the case of this study, 25 participants will be needed to guarantee an alpha of .05 and 80% statistical power, with no continuity correction. Therefore, we aim to recruit 30 participants to mitigate potential exclusions from the analysis set.

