#### Secondary Outcomes

The secondary outcomes of Phase I are hematological test abnormalities within the observation period. The secondary outcomes of Phase II are development of grade 2 or higher HFSR within 6 weeks of sunitinib therapy, progression-free survival and time-to-treatment failure of sunitinib therapy, dermatological abnormalities of the palmar or plantar surfaces within the observation period, and development of grade 2 or higher HFSR within 3 weeks after completion of the investigational treatment. HFSR and dermatological abnormalities will be evaluated by qualified dermatologists.

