#### Dermatological Abnormalities

Dermatological abnormalities will be defined as grade 1 or higher dermatological events, including bullous dermatitis, dry skin, erythroderma, pruritus, purpura, rash maculopapular, skin hyperpigmentation, and skin hypopigmentation, as specified by the CTCAE, version 4.0. Dose-limiting toxicities will be defined as grade 2 or higher events. If dose-limiting toxicity is more than 40% and is confirmed to be causally connected to the use of the investigational preparation, the study will be terminated and will not advance to Phase II.

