#### Primary Analysis

In the Phase I study, the safety of the investigational preparation will be evaluated at the end of two cycles of sunitinib therapy. If 2 or more participants out of 5 (≥40%) show dose-limiting toxicities during the above safety evaluation period or if the fifth participant is confirmed to have started the investigational preparation normally, ongoing Phase I enrollment will stop. At this time, the study secretary and principal investigator will discuss and determine the safety of the investigational preparation, based on the eCRF that records safety evaluation data.

The null hypothesis of the Phase II study has been defined as the frequency of development of HFSR of any grade (ie, grades 1-3) is 33.3% [18], and the frequency of development of HFSR of any grade (ie, grades 1-3) in one sample is analyzed with a significance level of 5%.

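### Five Phase I patients can support a decision to continue, but not the statement that the cream's safety has been confirmed

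*Protocol article*

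**What the plan says.** All references are to the protocol article.

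- **Study Objectives** makes dermatological safety the Phase I primary objective. **Primary Outcomes** defines the outcome as palmar or plantar skin abnormalities within two sunitinib cycles (6 weeks).
- **Sample Size Calculation** acknowledges that "there are no practical safety data pertaining to the administration of Amitose DGA-containing cream to patients with RCC receiving sunitinib therapy". It gives no statistical basis for the cohort of five: "The sample size for the Phase I study was primarily based on the extent of necessity and concernment". It then states: "In this study, the safety of Amitose DGA has been confirmed by a cohort of 5 patients". No event count or interval accompanies the statement.
- **Dermatological Abnormalities** counts grade 1 or higher events as abnormalities and grade 2 or higher events as dose-limiting toxicities (DLTs). The study ends without entering Phase II under this condition: "If dose-limiting toxicity is more than 40% and is confirmed to be causally connected to the use of the investigational preparation".
- **Primary Analysis** places the limit differently. Phase I enrolment stops on this condition, among others: "If 2 or more participants out of 5 (≥40%) show dose-limiting toxicities". The study secretary and principal investigator then discuss and decide on safety.
- **Secondary Outcomes** lists, for Phase II, "dermatological abnormalities of the palmar or plantar surfaces within the observation period". **Safety Endpoints** lists the same skin events without restricting them to a phase. Table 1 schedules dermatological examinations at screening, week 3 and week 6.

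**The concern.** The sentence on confirmed safety is a positive claim about a primary objective, made on five patients in a population for which the article says no practical safety data existed. It is not a detail left for a fuller document to supply.

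Passing a small stop/go check and establishing safety are different things. The first needs only that the observed count stayed below a limit. The second needs the data to make an unacceptable rate implausible, and the only rate that the article treats as unacceptable is 40% DLT. If the claim is carried into the trial report, the first primary objective will be answered with data that are compatible, at the usual 95% level, with rates above that limit.

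**Working it through.** **Inputs.** Cohort size 5 (Sample Size Calculation). Limit 40% DLT, where a DLT is a grade 2 or higher event (Dermatological Abnormalities, Primary Analysis). Total sample 30, including the first five (Sample Size Calculation). The two-sided 95% level is stated only under Secondary Analysis; using it for Phase I is an assumption, so other levels are shown. The Phase I count is not reported; 0/5 is taken as the best case and 1/5 as the next.

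**The plan's own figure.** 2/5 = 40%, as Primary Analysis states. The cohort size of 5 has no stated derivation, so there is nothing further to reproduce.

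**Step 1: what five patients can exclude.** For 0 events in n, the exact (Clopper-Pearson) upper limit is 1 − α^(1/n):

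- one-sided 95%: 1 − 0.05^(1/5) = 45.1%
- two-sided 95%: 1 − 0.025^(1/5) = 52.2%
- one-sided 90%: 1 − 0.10^(1/5) = 36.9%

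For 1 event in 5, the upper limit is the p that solves (1 − p)^5 + 5p(1 − p)^4 = α.

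| Result | One-sided 90% | One-sided 95% | Two-sided 95% |
|---|---|---|---|
| 0/5 | 36.9% | 45.1% | 52.2% |
| 1/5 | 58.4% | 65.7% | 71.6% |

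The method matters too. The Wilson upper limit for 0/5 is 43.4% (two-sided 95%) or 35.1% (one-sided 95%), but that approximation is unreliable at n = 5.

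**Step 2: how often a true 40% DLT rate stays below the limit.** With X binomial (5, 0.4):

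- P(X = 0) = 0.6^5 = 0.078
- P(X = 1) = 5 × 0.4 × 0.6^4 = 0.259
- P(X = 2) = 10 × 0.4² × 0.6³ = 0.346

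Under Primary Analysis (2 or more of 5 stops), P(X ≤ 1) = 0.078 + 0.259 = 0.337, or 34%. Under Dermatological Abnormalities (more than 40%, so 2/5 does not stop), P(X ≤ 2) = 0.337 + 0.346 = 0.683, or 68%. The two sections give opposite answers at exactly 2/5, and that single outcome doubles the probability.

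These figures treat every counted event as qualifying. Dermatological Abnormalities also requires a confirmed causal link. If 40% is read as the rate of all grade 2 or higher events, and only some are judged causal, the chance of not stopping is higher than 68%.

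**Step 3: what all treated participants can show.** Exact two-sided 95% upper limits:

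- 0/30: 1 − 0.025^(1/30) = 11.6%
- 3/30: 26.5%

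Both counts are illustrations. Both limits lie well below 40%.

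**The case against.** The strongest reply is that the benchmark is not the plan's. Nowhere does the article say that five patients are meant to exclude a 40% rate statistically. The limit is a stop/go rule on the observed proportion, and the cohort size is openly non-statistical. The disputed sentence stands in a sample-size paragraph beside past-tense enrolment text ("Participants were enrolled in the Phase I cohort group until the sample size reached 5 patients"), so it may be loose wording for a gate that was passed. The abstract still describes the study as designed to evaluate safety. All of this stands, and it limits the point to what may be concluded from the cohort. It does not rescue the word used, because passing a gate is not confirmation.

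The result also depends on the level chosen: at one-sided 90%, 0/5 does fall below 40%. That is why the level is named throughout. With 1/5, none of the exact limits shown falls below 40%.

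A reader might infer three stronger criticisms, which the document does not support:

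- *That skin safety in the full sample counts only as an unadjusted Phase II secondary outcome.* Safety Endpoints lists the same events without limiting them to a phase. The sentence declining multiplicity adjustment concerns efficacy, and adjustment has no bearing on a descriptive safety rate.
- *That 34% is the chance of an unacceptable cream entering Phase II.* It holds only on the Primary Analysis reading, leaves out the causality condition, and ignores that the final decision is a discussion rather than a count.
- *That the Phase I primary outcome must be redefined.* With 21 participants recruited, that would be a disruptive change, and it is unnecessary.

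**Conclusion.** The point holds as a correction to the safety claim and to the basis of the trial's safety conclusion. At the 95% level with exact limits, the best possible Phase I result leaves DLT rates up to 45.1% (one-sided) or 52.2% (two-sided) compatible with the data, against a limit of 40%. A result of 1/5 leaves 65.7% or 71.6%. The calculation assumes the 95% level and a count of 0 or 1, neither of which is given for Phase I.

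Separately, the two statements of the 40% limit conflict at exactly 2/5 and must be reconciled. Which of them is right is for the trial team to settle.

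Nothing here shows that the cream is unsafe or that the two-stage design is invalid. The 40% limit concerns grade 2 or higher events, whereas the Phase I primary outcome is any grade 1 or higher abnormality, so a result below the DLT limit does not by itself describe the primary outcome.

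**What to change.** 1. Replace the claim of confirmed safety with a statement that the Phase I stopping criterion was not met in 5 participants, if that is what occurred. Report the Phase I count with an exact 95% interval.
2. Keep the five-patient result as the gate to Phase II.
3. Base the trial's dermatological safety conclusion on all treated participants (about 30). Report grade 1 or higher events (the primary outcome) and grade 2 or higher events (the DLT) separately, each with an exact 95% interval.
4. Reconcile Dermatological Abnormalities and Primary Analysis at exactly 2/5, and state whether the causality condition applies to both.

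**Cost.** No new data are needed, since skin examinations at weeks 3 and 6 are already scheduled. The price is one documented added analysis, with Ethics Committee approval if it counts as a substantial amendment, and a more modest safety statement. The Phase I primary outcome stays as defined.

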#### Primary Analysis

In the Phase I study, the safety of the investigational preparation will be evaluated at the end of two cycles of sunitinib therapy. If 2 or more participants out of 5 (≥40%) show dose-limiting toxicities during the above safety evaluation period or if the fifth participant is confirmed to have started the investigational preparation normally, ongoing Phase I enrollment will stop. At this time, the study secretary and principal investigator will discuss and determine the safety of the investigational preparation, based on the eCRF that records safety evaluation data.

The null hypothesis of the Phase II study has been defined as the frequency of development of HFSR of any grade (ie, grades 1-3) is 33.3% [18], and the frequency of development of HFSR of any grade (ie, grades 1-3) in one sample is analyzed with a significance level of 5%.

#### Secondary Analysis

Secondary analysis on the efficacy of the investigational preparation throughout the whole observation period will be performed for additional discussion on the primary analysis, but multiplicity will not be adjusted in this analysis. Hypothesis testing will be performed with a two-sided 5% significance level and a two-sided 95% CI.

Logistic regression analysis, setting the development of HFSR as the dependent variable, will be performed by examining independent variables, including patient characteristics, sunitinib dose, and plasma concentrations of sunitinib, with a two-sided significance level of 5% and a two-sided 95% CI. Moreover, progression-free survival and time-to-treatment failure will be determined using the Kaplan-Meier estimate; medians and 95% CIs will be calculated.

We will carry out imputation for missing data by multiple imputation, as appropriate. Primary analyses will be performed by intention-to-treat analysis. Secondary analyses will consider per-protocol set, including participants who completed the treatment according to the scheduled protocol.

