### Study Procedure

The study schedule is shown in Table 1. Screening tests will be performed within 1 week of obtaining informed consent and researcher confirmation of each patient’s eligibility. Eligible patients will be enrolled via electronic case report forms (eCRFs).

Baseline data will be corrected beginning on the initial day of investigational cream usage. Patient-specific data (ie, sex, height, weight, concomitant diseases, medical history, prior chemotherapy, etc) and hematological and biochemical test data will be acquired from patients’ electronic medical records as per usual care practice information. The baseline dermatological status of each participant will be determined from the screening test.

Patients will receive sunitinib for 2 weeks, followed by a 1-week interruption; therefore, the therapeutic cycle lasts for 3 weeks. The initial dosage of sunitinib will be 37.5 mg/day. The participants will begin treatment with Amitose DGA-containing cream simultaneously with the start of sunitinib therapy. Plasma concentrations of sunitinib will be measured 10-14 days after the start of sunitinib therapy, as per usual care practice. HFSR will be checked regularly by the hospital urologists during the first 2 weeks of sunitinib therapy; during this period, the patients will remain in hospital.

During week 3 and week 6 outpatient clinical visits, participants will receive dermatological examinations by a dermatologist. This examination will focus on dermatological abnormalities of the palmar or plantar surfaces to assess the safety of the Amitose DGA-containing cream in Phase I. The dermatologist will additionally assess the efficacy of the Amitose DGA-containing cream at these visits during Phases I and II.

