## Discussion

HFSR is not a life-threatening side effect of multiple-TKIs but can drastically decrease quality of life and adherence to chemotherapy. This is the first clinical study of an Amitose DGA-containing cream in patients with RCC receiving sunitinib therapy. Moreover, this may be the first clinical study to use cosmetic preparations to determine dermatological adverse events induced by anticancer agents. This study will inform future, novel, prevention methods for HFSR.

We have reported the effects of ascorbic acid derivatives on keratinocyte toxicity induced by multiple-TKIs in vitro [13]. We verified these effects using an animal-testing alternative, consisting of a reconstructed human epidermal model in vitro. This methodological approach has also been used to evaluate dermatological adverse events [19-21]. Our experiment was conducted using similar methods; however, our results are preliminary and require further validation. Considering the evidence from our previous study, we aimed to evaluate both the effects of ascorbic acid derivatives alone on HFSR and the effects of combination therapy involving ascorbic acid derivatives and an existing standard-of-care prophylaxis.

The subjects of this study are patients receiving sunitinib therapy, not including other multiple-TKIs. We selected a single-arm, open-label design to maximize subject exposure and increase the likelihood of achieving study endpoints. Given our limited study population, the results of this study will be clear but the insights gleaned will be limited in their potential application.

Results from our previous study indicated that sunitinib-induced HFSR is likely to develop within 6 weeks of sunitinib initiation [22]. In this study, HFSR evaluated at weeks 3 and 6 was considered induced by sunitinib. Because sunitinib-induced HFSR also develops in latter phases, longer observation periods should be considered. Because adverse events related to sunitinib can cause dose reduction and interruption [23,24], the primary endpoint was set within two therapeutic cycles, considering study feasibility and clarity of results.

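### With about 3 HFSR events expected, the planned logistic regression is likely to be unreliable, and sunitinib dose is a poor predictor because it can be a result of the outcome

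*Protocol article*

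**What the plan says.** Secondary Analysis makes development of HFSR the dependent variable of a logistic regression that "will be performed by examining independent variables, including patient characteristics, sunitinib dose, and plasma concentrations of sunitinib". The tests are two-sided at 5%, with 95% CIs. The same section says that secondary analyses will consider the per-protocol set. It does not limit the number of covariates, does not say whether they enter together or singly, and names no method for sparse events.

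Sample Size Calculation fixes the scale: "The sample size for the Phase II study will be 30 participants", and "we estimate that the frequency of HFSR of any grade (ie, grades 1-3) among patients using the investigational preparation will be 10" percent.

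On dose, Study Procedure states: "The initial dosage of sunitinib will be 37.5 mg/day". The Discussion explains later changes: "Because adverse events related to sunitinib can cause dose reduction and interruption". The Abstract (Background) adds that HFSR itself can lead to interruption or a lower dose.

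**The concern.** There are two separate problems.

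**Too few events.** In logistic regression the information comes mainly from the rarer outcome. With about 3 events, a covariate or combination of covariates can easily separate patients with HFSR from those without. Maximum likelihood then has no finite solution: the software reports a huge odds ratio with a meaningless CI, or fails to converge. The plan names several patient characteristics plus dose and concentration.

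**Dose.** A starting dose shared by everyone has no variation, so its coefficient cannot be estimated. Dose received later can vary, but the document gives adverse events, HFSR among them, as the reason. A dose measured after HFSR begins may therefore be a result of the outcome it is meant to predict.

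At stake is the usefulness of the exposure–HFSR analysis. The Discussion itself treats the link between plasma concentration and HFSR as important.

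**Working it through.** **Inputs from the Protocol article.** N = 30; historical any-grade rate ("HFSR of any grade (ie, grades 1-3) was 33.3" percent); grade 3 rate ("HFSR of grade 3 was 2.2% among patients with metastatic RCC"); assumed 75% prevention of grade 1–2 HFSR; expected rate on the cream 10%; one starting dose of 37.5 mg/day.

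**Inputs assumed.** Number and type of covariates, binary prevalence 0.4, independent covariates, no true association. None of these is in the document.

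**Step 1: the plan's own figures.**
- Expected rate: 33.3 − 0.75 × (33.3 − 2.2) = 33.3 − 23.3 = 10.0%. Reproduced.
- Sample size, two-sided one-sample z-test without continuity correction: n = [(1.960 × √(0.333 × 0.667) + 0.842 × √(0.10 × 0.90)) / (0.333 − 0.10)]² = 25.5. The plan gives 25 ("25 participants will be needed to guarantee an alpha of .05 and 80% statistical power, with no continuity correction"), which is close enough to confirm the design inputs.

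**Step 2: events at the design assumption.**
- Expected: 30 × 0.10 = 3.0. With 25 analysable participants: 2.5.
- Binomial(30, 0.10): P(0) = 0.9³⁰ = 4.2%; P(≤3) = 64.7%; P(≤5) = 92.7%.
- If two characteristics, dose and concentration were entered together: 3 / 4 = 0.75 events per covariate.

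**Step 3: how often no finite fit exists.** Datasets of 30 with exactly 3 events were simulated (1,000 per setting in the first run), and complete or quasi-complete separation was tested by linear programming. The range is over repeat runs.

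| Covariates entered together | No finite solution |
|---|---|
| 2 continuous + 1 binary | 27–30% |
| 2 continuous + 2 binary | 47–49% |
| 3 continuous + 2 binary | 51–55% |

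For one binary covariate alone, all 3 events fall in the same level with probability 0.4³ + 0.6³ = 28%. So the binary covariate accounts for nearly all of the first row. The figure is 0.3³ + 0.7³ = 37% at prevalence 0.3 and 0.5³ + 0.5³ = 25% at 0.5.

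**Step 4: sensitivity to the assumptions.**
- With exactly 3 events and 1 to 3 continuous covariates only, separation occurs in about 2% of datasets or fewer.
- With a random event count at 10%, binary prevalence 0.3 and 2 to 6 covariates, no finite fit exists in 48–79% of datasets if types are mixed and 8–42% if all are continuous. These figures include the roughly 4% of datasets with no event.
- At the null rate of 33.3% (about 10 events), the mixed case falls to 3–14%. With exactly 10 events and prevalence 0.4 it is about 1–2%.

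**Step 5: dose, by reading the sections together.** Study Procedure gives one starting value, so its variance is zero. The Discussion and the Abstract give adverse events, including HFSR, as the only sources of change. Dose summarised over the six-week risk period therefore mixes exposure before HFSR with the response to HFSR.

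**The case against.** - **Joint entry is not stated.** This is correct, and the events-per-covariate figure applies only to a joint model. Fitting covariates singly largely removes the problem for continuous ones. It does not for binary ones, and the background data listed in Study Procedure include sex, concomitant diseases and prior chemotherapy.
- **This is a condensed article, and the covariate list and estimation method may be in an analysis plan that is not shown.** This is fair for the covariate list. But the article itself commits to the regression, the kinds of covariate (dose included), the test level and the CIs, and that choice fits badly with its own expected event count.
- **If the cream does not work there will be about 10 events and little separation.** This stands. But the plan should also work under the rate for which the trial was designed.
- **A dose reduction for another toxicity before HFSR is a real change in exposure.** This also stands. Whether dose follows the outcome depends on how and when it is measured, so this is a risk rather than a certainty.
- **The trough has a similar weakness.** HFSR is checked during the first 2 weeks and the sample is taken on days 10–14, so an early dose change could lower it. The fix allows for this.

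A reader might infer that the odds ratios and CIs will be infinite or strongly biased, or that the dose effect will come out reversed. Neither is supported. In the three joint settings of the table, 45–73% of datasets still gave finite estimates, and neither bias nor sign reversal was calculated.

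**Conclusion.** The concern holds in limited form. At the protocol's own 10% rate the regression is likely to be unreliable. It has no finite maximum-likelihood solution in roughly 25–55% of datasets if several covariates including binary ones are entered together, and in about a quarter for a single binary covariate. These figures rest on exactly 3 events, a binary prevalence of 0.4 and no true association, all of which are working assumptions except the expected count. The problem is rare with a few continuous covariates or with about 10 events. The dose point rests on the text alone: starting dose carries no information, and dose measured after HFSR onset can be a result of HFSR.

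This is a secondary analysis, intended to add to the discussion of the primary one. The one-sample primary test and the sample size are unaffected. It is worth correcting before the data are analysed, but it does not threaten the main conclusion.

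**What to change.** Revise the regression paragraph in Secondary Analysis as follows:

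1. Label the analysis exploratory.
2. Use Firth-penalised (or exact) logistic regression with one pre-named predictor, the day 10–14 trough of sunitinib plus its metabolite. Report penalised-likelihood CIs with the Firth fit.
3. Do not use dose received over the HFSR risk period as a predictor. If dose is kept, count only dose before HFSR onset.
4. Flag any patient whose HFSR or dose change came before the trough sample.
5. Tabulate the remaining characteristics by HFSR status, without tests.
6. State that no model is fitted if there are no events, which has a 4.2% chance at the design rate.

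The cost is a change of wording and possibly software beyond the base SPSS named in the Statistical Plan. No extra patients or visits are needed. The loss is a mutually adjusted model, which about 3 events could not support.

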## Abstract

**Background:**

Hand-foot skin reaction (HFSR) is a serious side effect induced by multiple-tyrosine kinase inhibitors (TKIs). HFSR can cause treatment interruption or decreased dosing. HFSR also markedly decreases quality of life and is associated with the therapeutic efficacy of multiple-TKIs. Therefore, the management and prevention of HFSR is an important issue; however, an effective method for its prevention has not been established. Specific ascorbic acid derivatives can reverse multiple-TKI-induced keratinocyte growth and pathological changes in vitro.

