### Intervention

The participants will apply three fingertip units of Amitose DGA-containing cream all over both the palmar and plantar surfaces more than three times a day, within two treatment cycles (ie, 6 weeks) of sunitinib. They will also apply heparinoid or urea-containing cream as a standard preventive treatment for HFSR following application of the investigational cream. The participants will be instructed to apply the investigational cream to moist skin, such as when washing their hands or feet, during face washing, or after bathing. The participants will keep a personal diary to record the frequency of application of Amitose DGA-containing cream.

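### The only analysis set named for the secondary analyses is treatment completers, which lengthens time-to-treatment failure almost by definition and can distort the grade 2 or higher HFSR rate

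*Protocol article*

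**What the plan says.** The last paragraph of Secondary Analysis in the protocol article deals with analysis sets in two adjacent sentences. The first reads: "Primary analyses will be performed by intention-to-treat analysis". The second reads: "Secondary analyses will consider per-protocol set, including participants who completed the treatment according to the scheduled protocol". The article names no further set for the secondary analyses.

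The Phase II list under Secondary Outcomes includes "development of grade 2 or higher HFSR within 6 weeks of sunitinib therapy, progression-free survival and time-to-treatment failure of sunitinib therapy". Secondary Analysis says that the two time-to-event outcomes will be summarised by Kaplan-Meier medians with 95% CIs.

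The treatment to be completed is cream applied "within two treatment cycles (ie, 6 weeks) of sunitinib". Under Discontinuation of Study Subject Participation, a patient can be withdrawn when "the patient is unable to continue sunitinib therapy because of disease progression, complications, or adverse events induced by sunitinib or Amitose DGA-containing cream". Participation can also be ended when the compliance ratio for the cream falls below 70%. The abstract's Background adds: "HFSR can cause treatment interruption or decreased dosing".

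**The concern.** Completing treatment is known only after baseline, and the article's own reasons for not completing overlap with the outcomes to be analysed. The overlap is closest for time-to-treatment failure: stopping sunitinib early is both the event and the reason for leaving the set. Everyone kept in the set has by selection got through about 6 weeks without that event, yet the Kaplan-Meier clock would count those weeks. For grade 2 or higher HFSR the link is looser. It operates only if a patient with severe HFSR stops treatment and so drops out of numerator and denominator together.

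The effects of the cream on severe HFSR and on sunitinib's therapeutic outcomes are stated secondary objectives. In a single-arm trial there is no control group subject to the same selection, so the distortion would go straight into the reported estimates. Multiple imputation, which the same section mentions, does not repair this: patients outside a completer set are not missing values within it.

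**Working it through.** **Inputs from the article:** recruitment target 30; treatment period 6 weeks; CT typically every 8-12 weeks; any-grade HFSR 33.3% under the null and 10% expected with the cream; historical grade 3 HFSR 2.2%. The article gives no median for time-to-treatment failure or PFS, no grade 2 rate and no dropout rate, so there is no figure of the plan's own to reproduce on this point. The event rates below are assumptions, shown over a range.

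**Time-to-treatment failure.** Assume that (a) stopping sunitinib counts as the event, (b) a patient who stops before week 6 has not completed treatment, and (c) times are exponential with median m weeks from the first dose.

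- Share failing before week 6: 1 − 2^(−6/m).
- Among those who reach week 6, P(T > t | T > 6) = 2^(−(t−6)/m). Setting this to 1/2 gives a completers' median of m + 6.

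| Assumed m (weeks) | Fail before week 6 | Expected out of 30 | Completers' median (weeks) | Rise |
|---|---|---|---|---|
| 13 | 1 − 2^(−6/13) = 27.4% | 8.2 | 19 | 6/13 = +46% |
| 26 | 1 − 2^(−6/26) = 14.8% | 4.4 | 32 | 6/26 = +23% |
| 52 | 1 − 2^(−6/52) = 7.7% | 2.3 | 58 | 6/52 = +12% |

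The absolute shift is 6 weeks in every row; only its relative size depends on m. The schedule table shows the last sunitinib week of cycle 2 as week 5, so if completion were judged on sunitinib dosing alone, the shift would be nearer 5 weeks.

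**Grade 2 or higher HFSR within 6 weeks.** Direct counting:

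| Cases among 30 | Who leaves the set | Rate in completers |
|---|---|---|
| 3/30 = 10.0% | 2 of the cases | 1/28 = 3.6% |
| 5/30 = 16.7% | 2 of the cases | 3/28 = 10.7% |
| 5/30 = 16.7% | 3 of the cases | 2/27 = 7.4% |
| 3/30 = 10.0% | 4 patients, none a case | 3/26 = 11.5% |

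The last row shows that the direction can reverse. For scale, the design expects 0.10 × 30 = 3 patients with HFSR of any grade, and the historical grade 3 rate would give 0.022 × 30 = 0.66. Three cases of grade 2 or higher would therefore mean that every expected HFSR case was at least grade 2. Five cases lie above the expected any-grade count but below the 0.333 × 30 = 10 of the null. The HFSR rows show a mechanism; they are not forecasts.

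**PFS.** Only progression or death before week 6 is lost through the completer condition. The first routine CT comes at 8-12 weeks, so few progressions would be recorded by then. The Introduction also links HFSR with the efficacy of this drug class, so removing patients who stop because of HFSR could partly offset any upward bias.

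**Primary outcomes.** Any-grade HFSR within 6 weeks (Phase II) and dermatological abnormalities within two cycles (Phase I) are primary outcomes and so fall under intention-to-treat. A patient who stops because of severe HFSR still counts as an event in the main efficacy test.

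**The case against.** The strongest reply is that the sentence does not confine the secondary outcomes to completers. It says only that secondary analyses will *consider* the per-protocol set, and the section opens by presenting secondary analysis as further discussion of the primary one. That fits the usual layout of intention-to-treat as the main analysis with per-protocol in support, and a full analysis plan may say so. This stands in part: a supportive reading is possible. But the sentence follows directly on one that gives intention-to-treat to the primary analyses, and completers are the only set attached to the secondary ones. A sponsor who intends the supportive reading needs the same one-sentence correction.

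A second reply is that the completer condition is not automatic. Withdrawal is permitted rather than required, HFSR may lead to interruption or a lower dose without ending treatment, and the article does not say whether either breaks completion. This stands for HFSR. It does little for time-to-treatment failure, where stopping sunitinib is itself the event.

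A third reply is that the consequences are limited: the only stated null hypothesis concerns any-grade HFSR, and the two time-to-event medians have no stated comparator. The article also provides for efficacy and safety testing when the cream is permanently stopped. These points stand, and they limit the importance of the concern.

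A reader might go further and infer that every secondary outcome is biased in the cream's favour by construction. The documents do not support that. The PFS effect is probably small and may be partly offset, the HFSR effect can go either way, and dermatological abnormalities within 6 weeks are also a primary outcome and a safety endpoint.

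**Conclusion.** The concern holds in a limited form. As written, the article names only treatment completers for its secondary analyses. If that is followed:

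- **Time-to-treatment failure** is biased upward almost by definition, by about 6 weeks on the median under an exponential assumption (+12% to +46% for assumed medians of 52 down to 13 weeks). This rests on early stopping of sunitinib counting both as the event and as non-completion.
- **Grade 2 or higher HFSR** can be understated if affected patients stop treatment. Size and direction depend on who leaves, and the article gives no rate from which to predict either.
- **PFS** is probably little affected.

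It would be wrong to infer that the trial's main conclusion is compromised: the primary outcomes in both phases are intention-to-treat and count patients who stop early.

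**What to change.** Replace the sentence on the secondary analysis set with one stating that time-to-treatment failure, PFS and grade 2 or higher HFSR are analysed in all enrolled participants who started the cream; that time-to-treatment failure and PFS are counted from the first sunitinib dose; and that the per-protocol set is supportive for the HFSR outcomes only and is not used for time-to-treatment failure or PFS.

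The cost is one sentence in the protocol or analysis plan. It needs no new data and leaves the sample size unchanged. The downside is that the estimates may be less favourable.
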